## Abstract

Although the effectiveness of cardiac rehabilitation (CR) programs in secondary prevention is well-recognized, there is a lack of studies exploring the potential of mobile health to enhance educational interventions within CR. The objective is to assess the impact of a structured WhatsApp-assisted health educational intervention, in conjunction with the usual care, compared to the usual care alone among participants enrolled in a CR program. The trial will recruit 32 participants enrolled in a CR program, who will be randomly assigned to a structured WhatsApp-assisted health educational intervention plus usual care or usual care alone group. The intervention will span 4 weeks, with assessments at baseline, 4 weeks, and 3, 6, and 12 months. The primary outcome measure is the cardiovascular risk factors knowledge score. Secondary outcomes include physical activity levels, anxiety and depression, and quality of life. Expected results include improved knowledge of cardiovascular risk factors, increased physical activity levels, and better mental health outcomes in the intervention group. Additionally, an enhancement in the overall quality of life is anticipated. These findings are expected to underscore the value of integrating mHealth with traditional CR methods, potentially shaping future approaches in chronic disease management and prevention.

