### 3.2. Randomization and Masking

Randomization will be conducted after baseline assessment. The participants will be randomized into one of the two groups: WhatsApp-assisted health educational intervention with the usual care (intervention group) or the usual care (control group). We will employ permuted block randomization for participant allocation. This approach involves generating a randomized sequence using varying block sizes to assign participants to different treatment groups. This method ensures balanced group sizes and minimizes selection bias. To maintain methodological quality and safeguard this study’s integrity, an allocation concealment strategy will be utilized involving the use of sealed opaque envelopes. These envelopes will be sequentially numbered and prepared by an individual not involved in the enrollment or assessment of participants. They will only be opened by personnel separate from the envelope preparation and assessment processes, thereby maintaining the concealment of the allocation sequence until assignment and preventing potential biases. Evaluators and data analysts will be masked to treatment allocation; however, participants will not be masked. Furthermore, the evaluator responsible for initial assessments will be blinded to group assignments, ensuring an unbiased evaluation process. The therapist administering the intervention via WhatsApp will be different from the one providing usual care, reinforcing the independence of treatment delivery from the assessment process. This structure is designed to maintain the integrity of the study by separating roles and concealing group assignments from those conducting assessments. All team members involved in this study were trained on the importance of maintaining blinding and will be regularly monitored for compliance.

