### 3.10. Sample Size Calculation

The sample size was calculated considering the main outcome and a test for a comparison of means. This was based on the mean and standard deviation obtained in a previous study carried out by Tang et al. (2018) [19], a power of 80%, a significance level of 5%, and a 1: 1 ratio. Additionally, we doubled the sample size, anticipating possible losses to follow-up. The calculation was performed using the statistical software STATA 16.1. The result obtained was 16 participants per study group.

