### 3.11. Statistical Analysis

Descriptive statistics such as means and standard deviations or medians and interquartile ranges for continuous variables and frequency tables for categorical variables will be used.

The bivariate analysis will be carried out to evaluate the differences in the variables measured within each group and between the study groups using parametric or non-parametric tests.

To evaluate the changes through follow-up, a repeated-measures analysis of variance will be applied if data follow a normal distribution, or a non-parametric variance analysis (ATS) if data do not follow a normal distribution [33]. Multivariable generalized estimating equation (GEE) models [34] will be applied to determine the effects of group, time, and the interaction between group and time on physical activity levels.

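### The GEE analysis of physical activity lists group, time and group-by-time effects without saying which is the intervention effect or how baseline enters; a baseline-adjusted post-baseline contrast would be clearer and more powerful at no cost

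*Protocol article*

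**What the plan says.** Section 3.11 (Statistical Analysis) assigns GEE models to one outcome. They "will be applied to determine the effects of group, time, and the interaction between group and time on physical activity levels". The models are called multivariable, but no covariates are listed. The preceding sentence describes the longitudinal aim for the outcomes in general: "To evaluate the changes through follow-up, a repeated-measures analysis of variance will be applied if data follow a normal distribution", with a non-parametric alternative otherwise.

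The Abstract gives the schedule as five assessments, "with assessments at baseline, 4 weeks, and 3, 6, and 12 months". Section 3.2 states that "Randomization will be conducted after baseline assessment". The Abstract also places physical activity among the secondary outcomes: "Secondary outcomes include physical activity levels, anxiety and depression, and quality of life".

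The article does not say whether baseline physical activity is a repeated outcome or a covariate in the GEE, how time is coded, or which term answers the comparison of the intervention with usual care.

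**The concern.** The baseline visit comes before randomisation, so the intervention cannot produce a difference between arms there. If that visit is one of the levels of time in a group-by-time model, the term labelled *group* does not estimate the intervention effect. Under one coding it is the baseline difference alone. Under the other it is an average that includes a visit with no possible effect.

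Because the plan lists three effects side by side without ranking them, a reader of the results could take a significant group term as evidence of efficacy when it reflects chance imbalance. A small group term could equally be taken as absence of effect. With 16 participants per arm, chance imbalance can be large. The question is also one of efficiency: the baseline measurement is already collected, and how it is used changes the power considerably.

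**Working it through.** **Inputs from the article.** 16 participants per arm (Section 3.10); one visit before and four after randomisation (Abstract, Section 3.2); model terms group, time and group-by-time (Section 3.11).

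**Assumptions not in the article.** Outcome analysed on a continuous scale with SD 1; constant post-baseline effect d = 0.8 SD; the same correlation ρ between any two visits (compound symmetry), 0.6 with a range of 0.4 to 0.7; complete data; two-sided 5% test with 30 degrees of freedom. The plan gives no figure for this analysis that could be reproduced.

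**Step 1: what the group term estimates if baseline is a repeated outcome.**
- Baseline as reference visit, interaction in the model: the coefficient is the baseline difference between arms, with expected value 0. Its standard error is √(2/16) = 0.354 SD, so chance alone gives a 95% range of ±1.96 × 0.354 = ±0.69 SD.
- Averaged (sum) coding, or no interaction: the coefficient is the mean over five visits, (0 + 4d)/5 = 0.8d, or 80% of a constant effect. If the effect fades as 1, 0.75, 0.5, 0.25, the result is 2.5/5 = 50% of the initial effect. The post-baseline average is then 2.5/4 = 0.625, and 0.5/0.625 is again 80%.

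**Step 2: check by simulated GEE.** Exchangeable working correlation, 16 per arm, five visits, ρ = 0.5, true effect 1.0 SD, 400 replicates. Average estimates:

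| Term | Average estimate |
|---|---|
| Group, baseline as reference visit | 0.01 |
| Group, averaged coding or no interaction | 0.80 |
| Mean of the four group-by-visit interaction terms | 0.99 |
| Group, post-baseline visits only, baseline as covariate | 0.99 |

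The last row matters: if baseline is a covariate, the group term is a valid intervention effect averaged over visits.

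**Step 3: power.** With V the per-person variance of the summary, the standard error of the arm difference is √(2V/16), and power comes from the noncentral t distribution.

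| Contrast | Effect | V | V at ρ = 0.6 | Power at ρ = 0.6 | Range, ρ 0.4-0.7 |
|---|---|---|---|---|---|
| Five-visit group term | 0.64 | (1+4ρ)/5 | 0.68 | 57% | 52-68% |
| Mean of four post-baseline visits, unadjusted | 0.80 | (1+3ρ)/4 | 0.70 | 74% | 70-84% |
| Interaction: mean post-baseline minus baseline | 0.80 | (1+3ρ)/4 + 1 − 2ρ | 0.50 | 87% | 72-95% |
| Mean post-baseline, baseline-adjusted | 0.80 | (1+3ρ)/4 − ρ² | 0.34 | 96% | 94-98% |

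Worked example, baseline-adjusted: V = 2.8/4 − 0.36 = 0.34; standard error √(2 × 0.34/16) = 0.206; noncentrality 0.8/0.206 = 3.88; power 96%. For the interaction contrast: V = 0.70 + 1 − 1.2 = 0.50; standard error 0.250; noncentrality 3.20; power 87%.

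Power for the first two contrasts falls as ρ rises; for the last two it rises. The baseline-adjusted contrast has the highest power at each correlation computed.

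**The case against.** The strongest reply is that the article does not commit the error. It never places baseline among the GEE outcomes, and a multivariable GEE could carry baseline as a covariate, in which case the group term is sound. It never calls the group term the intervention effect; listing the main effects and their interaction is a usual way to state the terms of a longitudinal model. The same sentence names the interaction, which does carry the effect when baseline is a repeated outcome and has about 87% power under the assumptions used here. Baseline handling and time coding are often left to an analysis plan, which is not shown.

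Most of this stands. A reader might infer that the plan relies on the wrong model term, or intends to report the group coefficient as its efficacy result. The document supports neither inference. It would also be wrong to say that a real effect must be missed, since that requires ignoring a term that the plan names.

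Two things remain. First, the five-visit reading is the likelier one: no baseline covariate is named, and the surrounding text is about change through follow-up, which a group-by-time model shows as change from baseline only if baseline is a level of time. Second, even on the favourable reading of the interaction, a better use of data already collected is available.

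The power figures also have a limit. Section 3.10 says "we doubled the sample size, anticipating possible losses to follow-up", so 16 completers per arm is the best case. Losses would lower every figure.

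**Conclusion.** The point holds as a clarification and a free improvement, not as an error in the plan. The listed group effect is interpretable as efficacy only if baseline is handled as a covariate, which the article does not say. If baseline is a repeated outcome, that term returns either 0% of the effect (with a chance range of ±0.69 SD) or 80% of a constant effect. The interaction is valid.

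The gain from baseline adjustment over the average interaction contrast is about 9 percentage points at a correlation of 0.6 (96% against 87%). It is about 22 points at 0.4 (94% against 72%) and about 3 at 0.7 (98% against 95%). The 0% and 80% results follow from the visit structure and coding. The power figures rest on an assumed effect size, correlation structure and complete follow-up. The reach is limited to physical activity, a secondary outcome; the GEE sentence does not cover the primary knowledge score.

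**What to change.** In Section 3.11, or in the analysis plan if one exists, state three things for physical activity:

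1. The intervention effect is the between-arm difference at named post-baseline visits, or their average, reported with a 95% CI.
2. Baseline physical activity is adjusted for, in one of two ways: as a covariate with only the four post-baseline visits as outcomes, or through a model with one common baseline mean for both arms and group-by-visit terms only after baseline. Either is acceptable.
3. No conclusion is drawn from a group main effect that includes the baseline visit.

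The cost is a few sentences and a different model statement. It needs no additional data, visits or participants. If the sponsor already intends baseline as a covariate, one sentence saying so, together with items 1 and 3, is enough.

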### 3.12. Ethical Considerations

The authors declare that the procedures will follow the ethical standards of the Committee of Responsible Human Experimentation, the World Medical Association, and the Declaration of Helsinki. The ethical principles of confidentiality, charity, non-malfunction, autonomy, and justice will be respected. The authors will obtain the informed consent of the recruited participants. This research was approved by the Universidad de Santander—Bucaramanga Research Ethics Board (Number: 023, 8 June 2021) and registered in the Australian New Zealand Clinical Trials Registry (ACTRN12622001446752).

### 3.13. Handling and Storage of Data

The data will be collected, processed, and stored in accordance with the policy for data handling as described in Law 1581 of 2012 of the Republic of Colombia [35], and their use will be exclusively for academic purposes. Electronic spreadsheets will be utilized for data entry, and Microsoft OneDrive will serve as the storage medium on a secure server provided by the university. All data will be treated confidentially and anonymized for the purpose of analysis. During and after this study, physical copies of the data and related documents will be securely kept in a locked file cabinet for 7 years.

## 4. Expected Results

This study aims to assess the effects of a structured WhatsApp-assisted health educational intervention on the knowledge of cardiovascular risk factors, physical activity levels, and mental health, including anxiety and depression, as well as the overall quality of life among participants in a CR program. Recognizing the proven effectiveness of CR in various clinical scenarios for patients with cardiovascular diseases, these programs will need to include health educational processes tailored to the participants’ needs.

Building on this foundation, our protocol will seek to evaluate the impact of CR by enhancing the educational component through technology. We will be utilizing WhatsApp, a free, widely used platform, to deliver this intervention. While the use of social networks for educational purposes is increasingly reported in the literature, publications in the Latin American context remain scarce. This presents an opportunity to showcase a low-cost community intervention strategy.

The educational strategy, designed to be delivered over four weeks, will align with the characteristics of CR programs in Colombia. These programs vary in frequency and duration but typically span at least a month. Our digital educational resources, animated and easy to understand, will have been validated by experts and the target audience. They will aim to provide clear, precise, relevant, truthful, timely, and updated information, covering the four most prevalent cardiovascular risk factors in Colombia: hypertension, diabetes mellitus, hypercholesterolemia, and smoking. The content will encompass physiology, medication, diet, physical activity, and emotional management.

We expect a notable improvement in participants’ understanding of cardiovascular risk factors due to the interactive and personalized nature of the WhatsApp-assisted educational intervention. The intervention group will likely show a significant increase in their cardiovascular risk factor knowledge score compared to the control group. Additionally, an increase in physical activity levels among participants receiving the intervention is expected. The daily engagement through WhatsApp, with its motivational messages and informative content, will likely encourage participants to adopt more active lifestyles, measurable through the IPAQ scores.

Another key expectation is the positive impact of the intervention on mental health. Although we acknowledge that increased awareness could potentially lead to anxiety if not properly managed, the structure of our intervention is designed to provide support and reassurance, thereby mitigating negative emotional impacts and promoting mental wellbeing. Therefore, we predict a reduction in anxiety and depression scores, as measured by the HADS, especially in the intervention group. The supportive nature of the intervention, coupled with regular information dissemination about cardiovascular health, is expected to alleviate participants’ stress and anxiety. Research has demonstrated that in anxious individuals, having more knowledge about their condition and prognosis can help modulate their behaviors in a positive way. For instance, de la Maza et al. (2015) [36] have shown that an educational program for parents of children with cancer not only increased their knowledge about the disease but also reduced their anxiety levels. Similarly, Çankaya and Şimşek (2021) [37] and Khalilzadeh Ganjalikhani et al. (2019) [38] support the notion that health education can effectively reduce anxiety, improve self-efficacy, and enhance the overall quality of life. Furthermore, an improvement in the quality of life, as reflected in the SF-36 scores, is also anticipated. The comprehensive educational content, which includes aspects like diet, exercise, and medication management, is likely to contribute to this overall enhancement in life quality.

An important aspect of this study will be the evaluation of the intervention’s sustained impact over time. We expect that the improvements in knowledge, physical activity, mental health, and quality of life will not only be evident immediately after the intervention but will also persist during the follow-up assessments at 3, 6, and 12 months. High adherence to the intervention is also anticipated, given the convenience and familiarity of the WhatsApp platform. The ease of receiving and interacting with educational content through a widely used app is expected to foster consistent participant engagement.

In conclusion, this study is poised to offer significant insights into the effectiveness of using a popular digital platform for health education in CR. The anticipated results are expected to align with the evolving landscape of digital health interventions in chronic disease management and prevention.

## Figures and Tables

**Figure 1 mps-07-00035-f001:**
[figure not shown]
Flowchart of this study.

## Data Availability

As this document is a protocol, there are currently no data available for sharing. Data and educational material will become accessible in accordance with this study’s progression and subsequent data collection phases.
